## Abstract

**Background:**

Urinary calculi (UC), affecting 1%‐13% globally, pose a significant health burden due to high recurrence rates (up to 50% within 10 years) and substantial health care costs. Adequate fluid intake is a cornerstone of prevention; yet, its adherence remains poor due to forgetfulness, lifestyle barriers, and limited patient education. Existing mobile health interventions for UC prevention often lack medical oversight and clinical validation. WeChat-based digital therapeutic intervention may have a positive effect on fluid adherence in this patient group.

**Objective:**

Our objective is to develop a WeChat applet to improve hydration behavior and reduce stone recurrence among postoperative patients with UC.

**Methods:**

This is an open-label, 2-arm, parallel-group randomized controlled trial. We will recruit 148 participants from China’s tertiary hospital and randomly allocate them in a ratio of 1:1 to the intervention or control group. The intervention group received standard postoperative care supplemented by the WeChat-Based Applet Fluid Intake Reminder (WAFIR), which delivers personalized fluid intake reminders, urine color monitoring, 24-hour fluid intake and urine output tracking, and evidence-based educational content on hydration and urolithiasis management. The control group receives standard care of general discharge instructions from nurses. The primary outcome is the fluid adherence, measured by 24-hour fluid intake and urine volume; secondary outcome measures are the Wisconsin Stone Quality of Life Questionnaire, Patient Health Questionnaire-9, Electronic Health Literacy Scale, physical activity (International Physical Activity Questionnaire—Short Form), and recurrence rate of UC. Outcomes are measured before intervention (T0) and after a 1-month (T1) and 3-month (T2) follow-up period. Intention-to-treat analysis, 2-tailed *t* tests, and repeated measures ANOVA will be used to compare outcomes; statistical significance is set at a *P*<.05 significance threshold. The study was approved by the ethics review board in December 2024.

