This study aims to investigate the efficacy of the WeChat-Based Applet Fluid Intake Reminder (WAFIR) in improving fluid intake among postoperative patients with UC compared to standard care, with the ultimate goal of reducing stone recurrence and enhancing patient well-being. The specific objectives are to quantify changes in daily fluid intake and urine output, evaluate its effect on the QoL, and determine its influence on readmission rates, recurrence rates, and eHealth literacy over the follow-up period. We hypothesize that patients receiving WAFIR exhibit statistically significant differences in 24-hour urine output (mL), fluid intake (mL/24 hours), QoL (Wisconsin Stone Quality of Life Questionnaire [WISQOL] score), eHealth literacy (Electronic Health Literacy Scale [eHEALS] score), or urinary stone recurrence rates (3-month follow-up) compared to those receiving usual care.

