##### 24-Hour Fluid Intake Volume

This measure is to calculate the participants’ fluid intake for a full 24-hour period. This comprehensive record should span a full 24-hour period, ideally starting and ending at the same time of day to standardize the assessment. Participants will be instructed to record the fluid consumed using either the WAFIR or another recording method, including water, tea, coffee, Chinese herbal tea, and other eligible liquids. The data on daily fluid consumption volume can be summarized automatically once patients log the data in the WAFIR in the intervention group. However, the participants must manually report the fluid intake volume in the control group. This is the direct parameter that reflects the adherence to fluid intake in the WAFIR.

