### Sample Size

An adequate sample size and statistical power ensure that the findings can be reliably generalized to a broader population. The required sample size for hypothesis testing is determined based on the expected effect size [38]. In this study, the sample size will be determined by a statistical tool, G*Power software (Heinrich Heine University Düsseldorf) [39], with an α of .05, a power of 0.80, and an allocation ratio of 1:1. The sample size for this study was calculated based on a comparable RCT that used an eHealth device (an intelligent water bottle) to promote increased fluid intake [18], of which the calculated Cohen *d* was 0.61, and the effect size is considered significant since Cohen *d* is over 0.5. Based on the calculations, a sample size of 92 participants is estimated. Accounting for an attrition rate of 38%, as observed in this research, a total of 148 participants are anticipated to be recruited.

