### Methods of Analysis

The study outcomes will be reported to adhere to the guidelines outlined in the CONSORT (Consolidated Standards of Reporting Trials) 2010 statements [44]. Statistical tests such as a 2-tailed *t* test and chi-square test will be used for continuous and categorical variables within 2 groups. The principal analysis will compare the fluid intake volume between the intervention and control groups using the 2-tailed *t* test. Secondary outcomes such as WISQOL, PHQ-9, and eHEALS will use repeated measures of ANOVA since they are measured over time and between 2 groups. If necessary, subgroup analyses will be conducted to explore whether the effect of the intervention varies across different demographic or clinical subgroups. Intention-to-treat analysis will be used to assess the impact of the treatment and its generalizability as well as the missing data. A planned interim analysis will be performed to evaluate both efficacy (whether the intervention shows sufficient benefit to potentially stop the trial early) and futility (whether the intervention is unlikely to demonstrate benefit if the trial continues) after 50% (74/148) of the target sample size have completed the primary end-point assessment. A significance level of *P*<.05 will be used to determine statistical significance, and all data analysis procedures will be conducted using the SPSS (version 26.0; IBM Corp) software package.

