## Discussion

This study represents, to our knowledge, one of the first RCTs to assess a nurse-led, WeChat-based DTx specifically tailored for UC management, addressing a critical gap in mHealth interventions that often lack medical oversight or clinical validation. The primary outcomes of this study are to evaluate the effectiveness of the WAFIR in improving fluid intake and urine output among postoperative patients with UC. We hypothesize that the WAFIR intervention, combining fluid intake reminders, urine color monitoring, fluid and urine tracking, and evidence-based educational content, will significantly enhance adherence to hydration recommendations compared to standard care, potentially lowering recurrence rates and improving patient-reported outcomes such as QoL (via WISQOL), eHealth literacy (via eHEALS), and mental health (via PHQ-9).

This study used face-to-face and telephone interviews to collect data. However, interviews are subject to limitations, including the absence of visual cues (particularly in telephone interviews), reduced ability to observe contextual details, and potential difficulties in eliciting sensitive information, which may affect data quality [45]. The primary outcome, 24-hour urine volume, is required to be collected. However, previous studies indicate challenges in obtaining precise 24-hour urine samples due to poor patient compliance, which may result in incomplete or abandoned collections stemming from the complex or inconvenient nature of the process, as well as deviations from the 24-hour collection period. To enhance the measurement accuracy of 24-hour urine collection, it is crucial to improve patient education on the importance of urine collection; simplify the collection process with clear guidelines, flowcharts, and user-friendly containers; and provide necessary tools like graduated urinals or collection bags. Regular monitoring and feedback sessions are essential to address any issues promptly. Additionally, incentivizing participation with rewards can boost patient motivation, ensuring higher compliance and accurate urine volume measurements within the specified time frame.

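### The primary outcome is named in conflicting ways and has no stated time point, while the sample size covers only one outcome at one time

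*Protocol article*

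**What the plan says.** The sections do not agree on the primary outcome.

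- **Abstract, Methods:** "The primary outcome is the fluid adherence, measured by 24-hour fluid intake and urine volume". No rule says how the two measures combine into adherence.
- **Outcome Measures, Primary Outcomes:** 24-hour urine volume and 24-hour fluid intake appear side by side. Of intake it adds: "This is the direct parameter that reflects the adherence to fluid intake in the WAFIR".
- **Methods of Analysis:** "The principal analysis will compare the fluid intake volume between the intervention and control groups using the 2-tailed *t* test". Urine volume is given no principal test.
- **Discussion, first paragraph:** "The primary outcomes of this study are to evaluate the effectiveness of the WAFIR in improving fluid intake and urine output".
- **Discussion, second paragraph:** "The primary outcome, 24-hour urine volume, is required to be collected".

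The Abstract and Data Collection define T0, T1 (1 month) and T2 (3 months), but neither follow-up time is tied to the principal comparison. The Introduction's hypothesis lists urine output, intake, quality of life and eHealth literacy, and ends "or urinary stone recurrence rates (3-month follow-up) compared to those receiving usual care". The Abstract and Methods of Analysis set significance at P<.05, with no order or division among outcomes or times. Sample Size uses one effect size (Cohen d 0.61), alpha .05, power 0.80 and 1:1 allocation: "Based on the calculations, a sample size of 92 participants is estimated". It raises this to 148 for 38% attrition, and names no test, outcome or time for the calculation.

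**The concern.** A protocol has to say which result decides the trial. Here a reader could take intake, urine volume, either or both as decisive, at 1 or 3 months. If the choice is made after the data are seen, or if any of these results may count, the stated 5% error rate does not hold. If alpha is divided, or both outcomes are required, the stated 80% power does not hold.

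The two measures are also not interchangeable. Intake is totalled by the applet in the intervention arm but reported manually by controls, whereas urine is voided into a graduated container. The trial is open-label and was registered after recruitment had started, so readers depend on this text to know what was fixed in advance.

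**Working it through.** **Inputs from the document.** d = 0.61, alpha .05, power 0.80, 1:1 allocation, 92 completers (46 per arm), 38% attrition and 148 recruited (Sample Size); two-tailed *t* test (Methods of Analysis); two outcomes and two follow-up times.

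**Inputs assumed.** d = 0.61 holds for each outcome and time. The document does not give the correlations, so a range is shown.

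**1. The plan's own size.** Power of a two-sided *t* test with n per arm comes from the noncentral *t* distribution with 2n−2 degrees of freedom and noncentrality d√(n/2).

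- n = 43: power 79.8%.
- n = 44: 0.61√22 = 2.861, power 80.8%. So 88 completers are enough.
- n = 46: 0.61√23 = 2.925, power 82.5%. This is the stated 92.
- Recruitment: 92/0.62 = 148.4, against 148 stated.

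The exact figure of 92 is reproduced by the Wilcoxon-Mann-Whitney option with relative efficiency 3/π (power 80.7% at 46 per arm, 79.8% at 45). For the *t* test named in the analysis section, 92 is four more than needed.

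**2. False-positive rate if any one result counts, each tested at .05.**

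| Routes to success | Independent | Correlated (assumed) |
|---|---|---|
| Two outcomes, one time | 1 − 0.95² = 9.75% | 7.8% at correlation 0.8 |
| Two outcomes, two times | 1 − 0.95⁴ = 18.5% | 12.8% at 0.8 between outcomes and 0.7 between times |

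The correlated figures are simulated. In the last cell, the correlation between different outcomes at different times is taken as 0.8 × 0.7 = 0.56. With one common correlation of 0.9 among all tests, the rates fall to 7.0% and 9.4%.

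**3. Power of 92 completers under rules that deal with two outcomes.**

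- Bonferroni over two (alpha .025): 74.0% per test. Reaching 80% needs 53 per arm, or 106 completers; 106/0.62 = 171 recruited.
- Both outcomes required at .05: by normal approximation one test has 83.3% power. Joint power is therefore 0.833² = 69.4% if independent, rising to 78.8% at correlation 0.9.
- One primary outcome at one time, the other next in fixed sequence: the first test keeps the full .05, so its power stays at 82.5%.

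**The case against.** The strongest reply is that the document does lean towards fluid intake. Methods of Analysis names a single principal test, the intake measure is called the direct parameter of adherence, eligibility is defined by intake, and the size is drawn from a trial that aimed to raise intake. The rules for alpha and test order may sit in an analysis plan that is not shown. This stands in part: it shows which reading to prefer, and the absence of an alpha rule is not itself the point. It does not remove the contradiction, because the Abstract, the outcome list and the Discussion say otherwise and no section fixes the time.

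Some stronger readings are tempting but not supported:

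- *The sample size fits no reading.* It fits one outcome at one time, with power to spare. It falls short only if alpha is split or both outcomes are required, and the document states neither rule.
- *The figure of 92 is an error.* Sample Size names no test, and 92 can be reproduced. Against the *t* test it is a small, conservative mismatch.
- *The Introduction's list joined by a disjunction is a decision rule.* No section uses it that way. It is loose wording that should be tidied.
- *The true error rate is nearly four times nominal.* That needs independence, which is implausible for intake and urine output in the same people.
- *Urine volume should be made primary.* The singular label rests on one Discussion sentence about collecting the sample, and the same section also names both outcomes and warns of incomplete collections.

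**Conclusion.** The point holds as a contradiction in the current text: the primary outcome is intake, urine volume or both depending on the section, and the decisive time point is unstated. The size supports one two-sided test at one time (82.5% power at d=0.61), but the document does not say consistently which test that is.

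If either outcome could carry the claim, the false-positive rate is about 8-10% at one time and 13-18.5% over two times, for correlations from 0.8 (outcomes) and 0.7 (times) down to 0. Power at 92 completers would be 74% under Bonferroni over two outcomes, and about 69-79% if both were required. The power figures assume d=0.61 for every test, which the document does not establish for urine volume or for each time. The planned interim look is a separate matter and is not included in these figures. The conflict must be resolved, because without that the claim of success is undefined.

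**What to change.** Reconcile the Abstract, the Introduction's hypothesis, Primary Outcomes, Methods of Analysis and the Discussion to one primary endpoint at one named time.

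1. Use 24-hour fluid intake, the stated principal analysis, unless the internal protocol that Trial Registration says was finalized before recruitment shows otherwise. Take the time point from that protocol too.
2. Disclose and date any choice made later. Recruitment is complete, registration was retrospective, and the document places the end of data collection in September or October 2025 and the analysis in December 2025. An undated change would look like outcome switching.
3. Test the other outcome (urine volume, if intake is first) next in fixed sequence at .05, and treat the other time point as supportive.
4. Replace the disjunctive hypothesis in the Introduction with this order.
5. State the size as 92 completers giving 82.5% power for that one two-sided *t* test at d=0.61, noting that 88 would be enough for 80%.

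No more patients are needed. The cost is that the second outcome loses equal primary status, plus the work of checking the text against the internal protocol.

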**Results:**

The development of WAFIR, conducted in collaboration with stakeholders, was finalized in February 2025. Recruitment commenced on March 1, 2025; data collection was completed in September 2025, and data analysis was analyzed in December 2025. Dissemination of findings is planned through conferences and publications in 2026.

**Conclusions:**

This research evaluates the effectiveness of a nurse-led, evidence-based digital therapeutic intervention, WAFIR, in overcoming fluid adherence barriers among postoperative patients following urolithiasis surgery, aiming to increase daily fluid intake and urine output, reduce recurrence rates, enhance quality of life, and generate empirical evidence for its application in urology care, thereby optimizing postoperative management within clinical settings.

## Introduction

Urolithiasis, or urinary calculi (UC), is emerging as a significant global health crisis, affecting individuals of all ages and genders. The prevalence of UC has been increasing worldwide over the past decades [1]. Estimated incidence rates are 7%‐13% in North America, 5%‐9% in Europe, and 1%‐5% in Asia [2]. In low-income countries, up to 25% of the population can be affected, often with fatal outcomes due to inadequate urological care [3]. In China, the prevalence of nephrolithiasis is around 5.8%, exceeding 10% in the southern region [4]. Meanwhile, the high recurrence rate of UC poses a significant challenge, with approximately 10%, 30%, and 50% of individuals experiencing recurrence at 1 year, 5 years, and 10 years, respectively [5-7]. The financial burden of UC is substantial, with yearly medical expenses estimated at 10 billion dollars in the United States and US $695.51 million in Europe [8,9]. Predictive models indicate that the high prevalence and recurrence rate will lead to a 25% increase in health care costs over the next 50 years [10]. This makes UC one of the most expensive urological diseases, highlighting the urgent need for better understanding and management of this condition.

The occurrence of UC is influenced by a variety of environmental, climatic, and dietary factors. Environmental and climatic conditions, particularly in hot climates, can contribute significantly to water loss and water quality issues. High temperatures often lead to increased perspiration, which in turn reduces overall water levels in the body. This dehydration can concentrate the urine, increasing the likelihood of stone formation. Additionally, water quality, specifically the levels of sodium and other minerals, plays a crucial role in this process [11,12]. Dietary habits are another critical factor in the development of urinary stones. Insufficient water intake is one of the primary dietary risk factors, as it leads to more concentrated urine, which facilitates the crystallization process. Poor dietary habits, such as the prolonged consumption of oxalate-rich foods—like spinach, nuts, and chocolates—significantly elevate the propensity for developing calcium oxalate stones [13]. High-sugar and high-fat diets further exacerbate this risk by influencing urinary elimination processes, making the urine more conducive to stone formation [14]. These risk factors highlight the important role of nurses in implementing targeted hydration protocols and dietary interventions to mitigate stone recurrence.

The European Association of Urology and the American Urological Association both strongly emphasize the importance of increasing fluid intake to prevent urinary stone formation. Research indicates that increasing fluid consumption stands out as a simple and economically feasible way to lower the risk of stone formation [15]. Then, McCauley et al [16] discovered that patients tend to be more open to increasing fluid intake than adopting other dietary or pharmaceutical therapies. Yet, Khambti et al [17] identified a challenge, noting that only about half of patients with urinary stones adhere to hydration recommendations, as determined through 24-hour urine output tests. Building on this, further research elucidated the underlying causes: at first, patients might not know or remember to drink enough; then, some dislike the taste of water or do not feel thirsty; and finally, the need for frequent voiding or workplace factors gets in the way [16]. Other research backs this up, showing that forgetfulness or not realizing their need for hydration plays a big role in poor fluid habits [18,19]. Therefore, enhancing adherence to fluid intake recommendations offers substantial benefits, including reduced health care expenditure through lower incidence of urinary stones and associated costs, improved public health outcomes, and an elevated quality of life (QoL) by decreasing the frequency and severity of symptoms.

Digital therapeutic interventions (DTx) deliver evidence-based, software-driven solutions via mobile apps, wearables, and web platforms to manage conditions. Unlike wellness tools, DTx is clinically validated, often regulated, and designed for measurable health outcomes [20]. By 2026, the global mobile app market was expansive, with approximately 4 million apps available on the Apple App Store and Google Play, reflecting the vast potential of digital health tools [21]. However, conventional mobile apps face significant barriers to widespread adoption, such as complex development processes, protracted timelines, and substantial financial investment, which often limit their scalability and accessibility in clinical settings. In contrast, WeChat applets, which require no installation and are integrated into China’s predominant social media platform, facilitate seamless, on-demand access, effectively addressing technical barriers and offering distinct advantages by enhancing user convenience and minimizing operational challenges. With over 1.4 billion monthly active users, WeChat has a vast reach and engagement, making it a widely used communication tool in China. Using WeChat’s existing infrastructure, the applets simplify the process by reducing the need for extensive coding and platform-specific adaptation and allow individuals to access them instantly. The significance of WeChat in health care has been amplified by its rapid adoption during the COVID-19 pandemic, which catalyzed its integration into various medical contexts, from telemedicine to patient education, markedly improving care quality [22,23]. Notably, the feasibility of using WeChat to enhance adherence to prevention strategies has been demonstrated among multiple chronic diseases [24]. WeChat-based DTx overcomes conventional mobile app barriers and drives health care innovation by enhancing patient adherence and care quality across diverse medical contexts, including chronic disease management and preventive strategies.

Previous studies have highlighted the limitations in the current landscape of DTx for fluid management and urinary stone prevention. Stevens et al [25] noted that many apps lack the support of medical professionals, leading to the dissemination of potentially false information and inaccuracies that could negatively impact patient health. This underscores the importance of involving medical professionals in the development and content review of these apps to ensure their reliability and clinical validity. The advent of digital technologies, such as wearable devices and intelligent water bottles, has introduced new methods for monitoring water intake and preventing urinary stones. However, the effectiveness of these devices is highly dependent on the practicality of their use. For instance, patients may not always have access to smart bottles in all settings, which can lead to incomplete fluid intake records. Karagöz and Sarıca [26] further pointed out that the high cost and inconvenience associated with these devices may deter long-term patient compliance, highlighting the need for more cost-effective and user-friendly solutions for fluid intake notification. A review of the literature reveals that most published studies are small-scale, single-arm pilot interventions lacking robust controlled trials designed to evaluate long-term effectiveness and adherence. Moreover, Philip-McKenzie et al [27] analyzed 51 apps from the Apple and Google Play Store and found that none of the apps measured urine volume and color, and only 1 provided medical advice or educational content regarding the consequences of poor hydration. This reveals a substantial gap in the provision of comprehensive medical advice and education within these apps to improve patients’ recognition of disease severity. Furthermore, Winoker et al [28] highlighted the scarcity of evidence supporting the benefits of mobile health (mHealth) interventions in urological care and emphasized the need for more rigorous research to validate the effectiveness of these technologies. Karagöz and Sarıca [26] also recommended that future research should focus on the practicality, security, efficacy, and overall benefits of these apps in preventing stone recurrence.

This study aims to investigate the efficacy of the WeChat-Based Applet Fluid Intake Reminder (WAFIR) in improving fluid intake among postoperative patients with UC compared to standard care, with the ultimate goal of reducing stone recurrence and enhancing patient well-being. The specific objectives are to quantify changes in daily fluid intake and urine output, evaluate its effect on the QoL, and determine its influence on readmission rates, recurrence rates, and eHealth literacy over the follow-up period. We hypothesize that patients receiving WAFIR exhibit statistically significant differences in 24-hour urine output (mL), fluid intake (mL/24 hours), QoL (Wisconsin Stone Quality of Life Questionnaire [WISQOL] score), eHealth literacy (Electronic Health Literacy Scale [eHEALS] score), or urinary stone recurrence rates (3-month follow-up) compared to those receiving usual care.

